## Abstract

**Background:**

Children displaying psychosocial problems are at an increased risk of negative developmental outcomes. Parenting practices are closely linked with child development and behaviour, and parenting programmes have been recommended in the treatment of child psychosocial problems. However, parental mental health also needs to be addressed when delivering parenting programmes as it is linked with parenting practices, child outcomes, and treatment outcomes of parenting programmes. This paper describes the protocol of a study examining the effects of a combined intervention of a parenting programme and a cognitive behavioural intervention for mental health problems.

**Methods/design:**

The effects of a combined intervention of Triple P Discussion Groups and Stress Control will be examined using a randomised controlled trial design. Parents with a child aged 3–8 years will be recruited to take part in the study. After obtaining informed consent and pre-intervention measures, participants will be randomly assigned to either an intervention or a waitlist condition. The two primary outcomes for this study are change in dysfunctional/ineffective parenting practices and change in symptoms of depression, anxiety, and stress. Secondary outcomes are child behaviour problems, parenting experiences, parental self-efficacy, family relationships, and positive parental mental health. Demographic information, participant satisfaction with the intervention, and treatment fidelity data will also be collected. Data will be collected at pre-intervention, mid-intervention, post-intervention, and 3-month follow-up.

**Discussion:**

The aim of this paper is to describe the study protocol of a randomised controlled trial evaluating the effects of a combined intervention of Triple P Discussion Groups and Stress Control in comparison to a waitlist condition. This study is important because it will provide evidence about the effects of this combined intervention for parents with 3–8 year old children. The results of the study could be used to inform policy about parenting support and support for parents with mental health problems.

**Trial registration:**

ClinicalTrial.gov: NCT01777724, UTN: U1111-1137-1053.

## Background

Young children displaying psychosocial problems (problems with behaviour, emotions, and relationships) are a significant public health concern due to the associated costs to the individual and society [1,2]. Of great concern is the large proportion of young children who display psychosocial problems. Prevalence rates from the Growing Up in Scotland (GUS) study found between 10-27% of children at primary school entry display emotional or behavioural problems considered to be outside the normal range, with conduct problems being the most prevalent difficulty [3]. As parenting practices are inextricably linked with child development and behaviour, parenting programmes have been recommended as the preferred treatment for young children displaying psychosocial problems [4].

Parents’ mental health is also linked with both parenting practices and child outcomes. Reports based on the GUS study stated that at any one time, approximately 12-16% of mothers of young children experienced mental health problems and that children with mothers with mental health problems were more likely to have negative behavioural, emotional, and peer outcomes than children whose mothers were without mental health problems [5]. It may be that parents’ inability to cope with mental health problems may limit their capacity to carry out effective parenting strategies and be positive in their interactions with their children [6].

Caring for a child with psychosocial problems can also be a depressing and stressful experience. Research has found that parents with a child who displays very difficult behaviour are more likely to report having a stressful or depressing parenting experience [7]. Other research has examined the relationship between parenting stress and child behaviour problems and found that parenting stress and child behaviour problems are both antecedents and consequences of one another, and therefore, have a mutually escalating effect over time [8], and that child behaviour problems predict a large amount of variance in parenting stress [9]. Furthermore, in efforts to manage difficult child behaviours parents use more coercive parenting practices [10]. It could be that less optimal parenting practices are an indirect outcome of parents’ limited capacity to cope with stress, including the stress related to dealing with their child’s psychosocial problems [6].

Previous researchers have suggested that parental mental health is particularly important to take into account when delivering parenting programmes as parents are responsible for implementing parenting strategies and modifying children’s behaviour [11]. There is also evidence that poorer parent mental health or parenting stress is associated with poorer treatment outcomes for children following parenting programmes [12-14]. This highlights the importance of addressing parents’ mental health alongside parenting practices when treating children displaying psychosocial problems.

One way to improve both parenting practices and parental mental health and maximise treatment outcomes of parenting programmes is to deliver parenting programmes in combination with a cognitive behavioural intervention aimed to improve mental health problems. There is some research that has examined the effects of combined interventions that target both parenting and mental health problems and reported reductions in dysfunctional/ineffective parenting practices, parenting stress, child problem behaviours, and improvements in parents’ mental wellbeing e.g., [15,16]. However, the interventions delivered in these studies are high-intensity interventions and take up a lot of individual practitioner time.

In contrast to high-intensity interventions, low-intensity interventions refer to programmes that require a low usage of practitioner time or usage of time in a cost-effective way, such as group based programmes [17]. Low-intensity interventions aim to increase access to evidence-based practice to enhance health and wellbeing on a population-wide basis [17]. Some low-intensity interventions are entirely untargeted, whereas others are targeted towards a particular group of individuals. To our knowledge, there is no research examining whether a combination of a low-intensity parenting programme and a low-intensity cognitive behavioural intervention for mental health problems would be effective in improving parenting practices, parents’ mental wellbeing, and children’s psychosocial problems. Thus the aim of the proposed study is to determine the effects of a low-intensity parenting programme (Triple P Discussion Groups, described below in the intervention section) and a low-intensity cognitive behavioural intervention for mental health problems (Stress Control, described below).

### Objective

This paper aims to describe the study protocol of a randomised controlled trial (RCT) of a combined intervention of Triple P Discussion Groups and Stress Control for parents with 3–8 year old children.

## Methods/design

### Design

The study is designed as a feasibility RCT (see Figure 1). First, informed consent will be obtained from all participants, followed by pre-intervention measures being administered. After pre-intervention measures are completed, participants will be randomly assigned to either an intervention or a waitlist condition. The intervention condition receives the combined intervention of Triple P Discussion Groups and Stress Control immediately after pre-intervention measures, whereas, the waitlist condition receives the intervention approximately 12 weeks later. To evaluate the effects of the intervention in comparison to a waitlist, participants in the intervention condition will complete questionnaire measures at mid-intervention and post-intervention. Participants in the waitlist condition will complete the same measures at the equivalent times. Participants allocated to the intervention condition will also complete questionnaire measures at 3-month follow-up. The National Health Service (NHS) West of Scotland Research Ethics Committee (REC ref 12/WS/0242) and the NHS Research and Development Management Office (R&D ref GN12FS463) have approved the study protocol and documentation.

**Figure 1 F1:**
[figure not shown]
Study design.

### Participants

Eligible participants will be parents/carers with a 3–8 year old child in Glasgow, Scotland. We aim to recruit 160 parents to participate in the study.

### Recruitment of study population

Advertising materials (a brochure, a poster, a flyer, and a blurb about the study) have been developed to inform potential participants of the study and encourage them to self-refer to participate. The advertisements will be disseminated to the local community in several ways: 1) the Stress Control website and members of the NHS Greater Glasgow and Clyde (GGC) STEPS Primary Care Mental Health Team (http://www.glasgowsteps.com), 2) GPs and health clinics in local community, 3) community health teams in the South Glasgow area (multi-disciplinary teams of social care, nursing, and health staff who provide support and advice to families with young children: http://www.chps.org.uk/glasgow), 4) local primary schools, nurseries, early years centres, and playgroups, 5) libraries, cafes, and shops in the local community, and 6) social media. The advertisements encouraged parents with 3–8 year old children who were *‘juggling a lot as well as being a parent’* and were interested in attending 8-week group programme aimed at helping parents *‘learn to relax, de-stress, and achieve Healthy And Positive Parenting for You’* to self-refer to take part. Upon contact, the researchers will inform parents interested in taking part of the study protocol and obtain informed consent. Recruitment of participants to the study will start in March 2013.

### Study inclusion and exclusion criteria

To take part in the study, participants must: 1) have a child between the ages of 3 and 8 years old (rationale: the content delivered in the Triple P Discussion Groups is relevant for parents with children between the ages of 3 and 8 years), 2) be able to attend the group sessions held at the Langside Halls in Shawlands, Glasgow, and 3) be able to read a newspaper without assistance (rationale: the written materials used in the Triple P Discussion Groups and Stress Control are not suitable for parents who cannot read a newspaper without assistance). Participants are excluded if the child has a diagnosis of a developmental or intellectual disability or other significant health impairment (rationale: the Triple P Discussion Groups are designed for children with psychosocial problems that are otherwise normally developing).

### Randomisation procedure

Randomisation occurs at the level of individual target children. A computer generated list of random numbers will be used to allocate to condition in sequence of completion of pre-intervention measures. Allocation to condition will be conducted by an individual independent of the study to ensure there is no bias in the allocation.

### Sample size

The Parenting Scale (PS) Total score and the Depression Anxiety and Stress Scales-21 (DASS-21) Total score were used to determine the sample size. For a 0.3-point difference between the two conditions at post-intervention on the PS Total score, given a standard deviation of 0.6 (an effect size of 0.5), 64 families per condition are required to achieve power of 80% at an alpha of .05. For a 5-point difference between the two conditions at post-intervention on the DASS-21 Total score, assuming a standard deviation of 10 (an effect size of 0.5), 64 families per condition are required to achieve power of 80% at an alpha of .05. Assuming expected attrition of 20%, an initial sample of 160 families is needed, thus 80 families in each condition. Table 1 displays the expected means and standard deviations for the PS Total and DASS-21 Total scores for the two conditions at pre- and post-intervention.

**Table 1 T1:** Expected mean and standard deviations for the primary outcome measures

	**Intervention condition**				**Waitlist condition**			
	**Pre-intervention**		**Post-intervention**		**Pre-intervention**		**Post-intervention**	
	***M***	***SD***	***M***	***SD***	***M***	***SD***	***M***	***SD***
Expected PS Total score	3.0	0.6	2.7	0.6	3.0	0.6	3.0	0.6
Expected DASS-21 Total score	18	10	13	10	18	10	18	10

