### Intervention

The intervention to be evaluated is a combination of Triple P Discussion Groups and Stress Control. The Triple P-Positive Parenting Program is a public health approach to preventing and treating emotional, behavioural and developmental problems displayed by children and adolescents [18] (http://www.triplep.net). This is achieved through increasing knowledge, skills, and confidence in parenting. Triple P uses a tiered system of intervention with five levels of increasing strength, ranging from information-based strategies delivered via the media (level 1) to intensive individually tailored multi-session programmes (level 5). Four meta-analyses examining the outcomes of Triple P interventions have demonstrated positive effects for child behaviour problems, parenting practices and self-efficacy, and parental wellbeing [19-22].

The Triple P Discussion Groups are a level 3, low-intensity intervention designed to provide specific advice about common child behaviour or developmental issues. The Triple P Discussion Groups are interactive in nature and are typically run with 10–20 parents. Previous research evaluating the Triple P Discussion Groups using randomised controlled trial designs has found that in comparison to a control group, participants in the intervention condition reported significantly fewer child behaviour problems, less dysfunctional/ineffective parenting practices, and greater parenting self-efficacy after attending the programme [23,24].

Two 120 minute Triple P Discussion Groups will be used in this study; the ‘Being a Positive Parent’ and the ‘Dealing with Disobedience’ Triple P Discussion Groups (see Table 2 for information about session content, duration, and delivery). All practitioners delivering the Triple P Discussion Groups will be trained in Triple P and standardised training is provided by Triple P International (for more information on training see: http://www.triplep.net).

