Stress Control is a low-intensity cognitive behavioural intervention that aims to promote mental health and wellbeing on a community-wide basis [25] (http://www.glasgowsteps.com). The central focus of Stress Control is to teach cognitive behavioural therapy techniques to help individuals cope with anxiety, depression, panic, poor sleep, and/or low self-confidence. The programme is didactic in nature, consists of six 90 minute group sessions, and is typically delivered to 30–100 people [25] (see Table 2 for information about session content, duration, and delivery). Research evaluating Stress Control using controlled trial designs and pre-post uncontrolled designs has found that Stress Control is effective in reducing participants’ anxiety, depression, and distress, and improves general psychological wellbeing [25-28]. The practitioners delivering the Stress Control sessions are staff from the NHS GGC STEPS Primary Care and Mental Health Team. The STEPS Primary Care and Mental Health Team provide a range of mental health services to individuals in South East Glasgow and Stress Control is delivered as part of their regular practice. All practitioners delivering the Stress Control sessions are trained to deliver the programme. Training and supervision is provided by the programme developer, [name], a member of the STEPS Primary Care and Mental Health Team.

**Table 2 T2:** Overview of intervention sessions

**Session**	**Content**	**Duration**	**Delivered by**
Being a Positive Parent Triple P Discussion Group	• Introduction to principals of positive parenting	120 minutes	Trained Triple P practitioners employed by the NHS GGC
	• Taught skills to support child’s competence and development, and build a positive relationship with their child		
Dealing with Disobedience Triple P Discussion Group	• Introduction to reasons for child disobedience and parenting traps		
	• Taught skills to encourage positive child behaviour and to manage disobedience		
Stress Control Session 1: Information about stress	• Introduction to Stress Control	90 minutes	Employees of the NHS GGC, STEPS Primary Care and Mental Health Team
	• Information about common mental health problems provided		
Stress Control Session 2: Controlling your body	• Introduction to how stress affects your body		
	• Taught skills to control your body		
Stress Control Session 3: Controlling your thoughts	• Introduction to how stress affects your thoughts		
	• Taught skills to control your thoughts		

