### Data analysis procedure

Descriptive statistics will be used to present participation and retention rates. Means and standard deviations will be presented for continuous outcome measures and frequencies and percentages will be presented for categorical variables. The pre-intervention characteristics of participants in each condition (intervention and waitlist) will be compared. Chi-squared tests will be used to compare any group differences for categorical variables and *t*-tests will be used for continuous variables. Missing data will be explored following data collection and depending on the amount and type of missing data, a range of methods may be utilised. It is likely that imputation techniques will be used to extrapolate missing data.

Univariate and multivariate analyses will be conducted to examine the effects of the combined intervention in comparison to the waitlist condition on changes in dysfunctional/ineffective parenting practices, parental mental health, children’s behaviour, parenting experiences, parenting self-efficacy, family relationships, and parental positive mental health. All analyses will use an intent-to-treat approach using data from all participants who completed pre-intervention measures. In addition to intent-to-treat analyses, per protocol analyses will be conducted using data from participants who attended at least one session of the intervention and who completed measures at more than one time point. SPSS will be used to conduct the analyses and estimates of effects will be calculated and reported using Cohen’s *d*. Reporting of the trial will follow the CONSORT guidelines.

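### The stated 80% power treats families as independent, but the intervention arm is treated in groups, so power falls short if outcomes correlate within groups

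*Protocol article*

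**What the plan says.** The sample size section of the protocol article sets out its calculation in full for both primary outcomes. The first input is a "0.3-point difference between the two conditions at post-intervention on the PS Total score, given a standard deviation of 0.6". The second is a "5-point difference between the two conditions at post-intervention on the DASS-21 Total score, assuming a standard deviation of 10". Each is an effect size of 0.5, and for each the article concludes that "64 families per condition are required to achieve power of 80% at an alpha of .05". It then allows for loss: "Assuming expected attrition of 20%, an initial sample of 160 families is needed, thus 80 families in each condition".

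On allocation, the Randomisation procedure section says: "Randomisation occurs at the level of individual target children". On delivery, the Intervention section describes the Triple P Discussion Groups as interactive and says they "are typically run with 10–20 parents". It describes Stress Control as didactic and says it "is typically delivered to 30–100 people". Under Waitlist condition, those families are offered the programme only after their post-intervention-equivalent questionnaire.

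On analysis, the Data analysis procedure section says: "Univariate and multivariate analyses will be conducted to examine the effects of the combined intervention in comparison to the waitlist condition". It names no outcome model and no group term. The chi-squared and t-tests mentioned there are for comparing pre-intervention characteristics.

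**The concern.** Individual randomisation followed by group delivery in one arm gives a partially nested design. Parents who attend the same sessions share practitioners, discussion and timing, so their later scores may be correlated. Waitlist families have no such link when the arms are compared. The variance of the intervention-arm mean then exceeds what 64 independent families would give, and the sample size section makes no allowance for this.

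Two things are at stake. The first is the power claim for the Parenting Scale (PS) Total and DASS-21 Total scores, which is stated without condition. The second is the validity of the comparison if it is analysed without regard to groups. The Discussion makes a larger trial depend on the combined intervention proving effective and mentions adoption into routine NHS practice, so the precision of the result matters even in a feasibility trial.

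**Working it through.** **Reproducing the plan's figure.** The inputs are d = 0.3/0.6 = 5/10 = 0.5, alpha 0.05 and power 80%. Sidedness is not stated; two-sided reproduces the figure, while one-sided would give 50 by the normal approximation. The exact two-sample t-test gives power 79.5% at 63 per arm and 80.1% at 64. Allowing for 20% loss, 64/0.8 = 80. The arithmetic is correct for independent families.

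**Adding grouping in the intervention arm only.** With m analysed families per group, the design effect in that arm is DE = 1 + (m − 1) × ICC. In SD units, the standard error of the difference is √((DE + 1)/64), against √(2/64) = 0.177 under independence.

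**Assumptions.** The article gives no ICC; 0.01 to 0.10 is assumed. It gives no group numbers for this trial. As an illustration, 80 intervention families in 5 groups of 16 leave 64/5 = 12.8 analysed per group after 20% loss.

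**Formulas.**
- Large-sample power = Φ(0.5/SE − 1.96).
- Few-groups power uses the noncentral t with Satterthwaite df, taking 5 − 1 = 4 df for the intervention arm and 63 for the waitlist arm.
- Type I error of a test that ignores groups = 2 × (1 − Φ(1.96/√((1 + DE)/2))).

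Worked case, ICC 0.05: DE = 1 + 11.8 × 0.05 = 1.59; SE = √(2.59/64) = 0.201; 0.5/0.201 = 2.49; large-sample power = Φ(2.49 − 1.96) ≈ 70%. Satterthwaite df ≈ 10.4, critical t ≈ 2.22, power ≈ 62%.

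| ICC | DE | Large-sample power | Power with few-groups df | Type I error if groups are ignored |
|---|---|---|---|---|
| 0 | 1.00 | 81% | 75% | 5.0% |
| 0.01 | 1.12 | 78% | 72% | 5.7% |
| 0.02 | 1.24 | 76% | 69% | 6.4% |
| 0.05 | 1.59 | 70% | 62% | 8.5% |
| 0.10 | 2.18 | 61% | 51% | 12% |

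The 81% at ICC 0 is the normal approximation; the exact t figure is 80.1%.

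**Sensitivity to group size.** At ICC 0.01 / 0.05 / 0.10, large-sample power is 79 / 72 / 65% for m = 10 and 77 / 64 / 53% for m = 20. Simulation of the unclustered test at ICC 0.05 gives type I error of 7.8% with 6 groups, 9.4% with 4 and 11.1% with 3, close to the formula. If Stress Control ran as two classes of 32 analysed families, and the class were the source of correlation, the formula gives 6.8 / 8.7 / 14 / 22% at ICC 0.01 / 0.02 / 0.05 / 0.10.

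**Interval width.** The ratio to the independent analysis is (t × SE)/(1.979 × 0.177), where 1.979 is the critical t on 126 df. At ICC 0.05 it is (2.218 × 0.2012)/(1.979 × 0.1768) ≈ 1.28. At ICC 0.01 it is about 1.12 and at ICC 0.10 about 1.46.

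**The case against.** A reader might infer that the trial will use an unclustered test and so has a type I error above 5%. The article does not support that. It names no outcome model, a random group term is consistent with its wording, and model detail is commonly left to an analysis plan, which is not shown. The inflation also depends on the null. If the programme affects no family, the shared-delivery effects are absent as well and the unclustered test stays near 5%. Inflation needs real group effects that average to zero. The type I figures are therefore conditional.

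Nor do the documents fix the size of the power loss. The ICC is not given, and the group sizes are typical for the programmes rather than planned for this trial. They count parents, whereas the Measures section encourages all carers to attend but takes outcomes from one, so there could be fewer families per group. The intent-to-treat set includes non-attenders, who share no group. Both points lower the design effect. At ICC 0.01 and groups of 10 to 20, the large-sample loss is only a few points.

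It would also be wrong to say that 80% holds exactly at ICC = 0. With five groups and Satterthwaite df, power there is about 75%, so part of the fall comes from the df method. Applying a design effect to both arms would overstate the problem, since the waitlist arm is ungrouped.

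Baseline adjustment may recover power, since both outcomes are measured before the intervention. A pre-post correlation of 0.5 multiplies the variance by 1 − 0.25 = 0.75. With the ICC unchanged, that restores about 80% large-sample power at m = 15 and ICC 0.05, but only about 74% in the five-group case with few-groups df. The article neither gives nor uses such a correlation, and adjustment alone does not remove correlation within groups.

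Finally, this is a self-described feasibility trial. That lowers the severity, but the article still states a formal 80% power for two primary outcomes.

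What remains is the sample-size point. That calculation is given in full, and a better analysis model would not make its independence assumption true.

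**Conclusion.** The point holds as a sample-size and disclosure problem and should be fixed. The 64 per condition is the independent-families figure with no margin, so the stated 80% is not delivered, on the calculation's own terms, if outcomes correlate within groups. Under the assumed five groups of about 13 analysed families, ICC 0.01 costs little in large samples (about 78%) and ICC 0.10 costs a great deal (about 61%); few-groups df lower these to about 72% and 51%. The direction needs only a positive ICC. The size rests on the assumed ICC and group numbers and on no baseline adjustment. Type I error of about 5.7% to 12% follows only if groups are ignored in the analysis and group effects exist.

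**What to change.** Leave N unchanged.

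1. In Sample size, state that the 80% assumes independent families and no baseline adjustment. Give power over an ICC range, for example 0.01 to 0.10, for the planned number of groups, using the same df method as the analysis.
2. Record each family's Triple P group and Stress Control class during delivery, since membership may be hard to reconstruct later. Analyse PS Total and DASS-21 Total with a linear mixed model that has a random group effect in the intervention arm only, waitlist families as singletons, small-sample df (Satterthwaite type) and the baseline score as covariate. SPSS, the software already named, can fit this.
3. If only one or two Stress Control classes run, state as a limitation that class effects cannot be separated from treatment. The model does not cure that case.

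The practical cost is a few sentences, two identifier variables and a different SPSS procedure. The scientific cost is a less favourable stated power and noticeably wider intervals: with five groups and before baseline adjustment, about 12% wider at ICC 0.01, 28% at ICC 0.05 and 46% at ICC 0.10.
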